# Sympathetic Nervous System and Exercise Affects Cognition in Youth (SNEACY): study protocol for a randomized crossover trial

**DOI:** 10.1186/s13063-021-05096-w

**Published:** 2021-02-18

**Keywords:** Brain function, Executive control, Neuroimaging, Physical activity, Children

## Abstract

**Background:**

There is an increasing prevalence of physical inactivity during childhood, which is associated with a variety of health problems. However, the mechanisms by which acute exercise benefits cognition in childhood remains unknown. Here we describe the protocol for a randomized crossover trial called SNEACY (*Sympathetic Nervous System & Exercise Affects Cognition in Youth*), a study designed to better understand mechanisms linking acute exercise and cognition in 9–10-year-old healthy, cognitively normal children.

**Methods:**

Children from the Greater Boston, MA region will be recruited to participate in this single center study. A randomized crossover design will be utilized, such that participants will act as their own controls, through initial randomization to condition assignment and condition counterbalancing across participants. One hundred three children will participate in three randomized acute interventions: moderate intensity treadmill exercise (20 min, 70–75% of their maximal heart rate), seated rest (20 min), and a Trier Social Stress Test for Children (14 min). These visits will occur on 3 three separate days, approximately 5–8 days apart. Before and after each intervention, children complete a variety of cognitive tasks measuring attentional inhibition while their neuroelectric activity is recorded. Variables of interest include EEG data, accuracy and reaction time, academic achievement, and salivary alpha amylase. Academic achievement is also assessed following interventions. In addition, children provide passive drool samples throughout the interventions to measure various biomarkers that may explain the acute exercise benefit on cognition.

**Discussion:**

The results from this study could influence educational and public health recommendations to enhance cognition and learning in pre-adolescent children.

**Trial registration:**

ClinicalTrials.gov NCT03592238. Registered on 19 July 2018

## Background

Despite widespread health campaigns, children have become increasingly inactive and unfit [1], with > 50% of children not meeting the daily recommended 60 min of moderate-to-vigorous physical activity (MVPA) [2]. Adverse effects of inactivity during childhood have been observed for their physical health [3], as well as their psychosocial well-being [4]. Inactivity during childhood tracks into adolescence and adulthood, resulting in earlier mortality and greater morbidity associated with chronic diseases including cardiovascular disease and type 2 diabetes. However, largely absent from public health concerns is the effect of physical inactivity on brain health and cognition. In contrast, there is a growing literature detailing the beneficial effects of physical activity (PA) on brain health, cognition, and academic performance [5–7].

In particular, growing evidence indicates that an acute bout of PA has beneficial effects on brain function, cognition, and scholastic achievement [8–10]. For example, 20 min of moderate intensity walking improves neural and behavioral correlates of inhibition and academic performance [8–10]. That is, following 20 min of walking, reports indicated that children exhibit enhanced brain function, improved cognitive performance during tasks demanding greater amount of inhibition, and higher academic achievement in mathematics and reading compared to 20 min of rest [9]. The technique used to measure brain function was event-related brain potentials (ERPs), a non-invasive measure of neuroelectric activity during task engagement and response selection. One ERP component, known as the P3, is related to the allocation of attentional resources [11, 12] and the speed of stimulus classification during stimulus engagement [13, 14].

However, minimal evidence exists regarding potential *mechanisms* underlying the transient effects of acute PA on brain and cognition. One potential mechanism involves phasic shifts in the sympathetic nervous system (SNS), as measured via the biomarker: salivary alpha-amylase (sAA). sAA is an enzyme produced by the salivary glands, which is modulated by physical and psychosocial stress as part of the first wave of the “fight or flight” response [15]. The second wave of the stress response involves the release of the glucocorticoid, cortisol from the adrenal cortex. sAA and cortisol have also been related to alterations in executive control functions (i.e., inhibition, working memory, cognitive flexibility) and academic achievement in children [16].

The SNEACY study was designed to address possible mechanisms by which acute PA acts on cognition and brain function (as measured by ERPs) in typically developing, healthy children. This lack of understanding constitutes a significant gap in the research, which is reflected in a rapid decline of PA opportunities for children throughout the school day. Thus, this study will examine the extent to which PA influences the cognitive and brain health of children. Results are expected to be particularly relevant to public health and education with potential implications for future policies aimed at improving physical and mental health during childhood. In particular, the primary goal of the SNEACY study is to discover the role of SNS activity as a mediator of the effects of a single bout of PA on brain function, cognition, and academic achievement in preadolescent children.

## Material and design

### Summary of aims

The objective of the SNEACY study is to test several aims: (1) Investigate basic laboratory and applied scholastic performance aspects of brain function, cognition, and academic achievement following aerobic exercise compared to active (i.e., Trier Social Stress Test for Children (TSST); a commonly used psychosocial stressor) and passive (i.e., seated rest) control conditions; and (2) Investigate phasic changes in SNS activation (as indicated by sAA) as a potential mechanism for the transient beneficial effect of exercise on brain function, cognition, and academic achievement. Phasic activation refers to brief, rapid changes in the SNS [17] in response to salient or task-relevant information in the stimulus environment [18]. Phasic sAA has been shown to be related with attention, memory, and various academic outcomes [16, 18–22]. SNEACY is a randomized crossover trial with three acute interventions: 20 min of moderate intensity treadmill exercise, 20 min of seated rest, and a 14-min TSST for Children. The TSST and seated rest interventions serve as active and passive control conditions, respectively, for the experimental intervention involving moderate intensity exercise. As a result of this design, changes observed in the aerobic exercise intervention can be attributed to the exercise component of the intervention rather than to other, potentially confounding factors, such as expectancy effects, stress, or elevated heart rate. The study will enroll and randomize 103 typically developing, 9–10-year-old children. We hypothesize that exercise-induced phasic increases in SNS activity, indicated by sAA levels, will mediate the effect of a single bout of exercise on brain function (i.e., P3 amplitude and latency), cognition (i.e., executive control), and standardized achievement test performance (i.e., mathematics, reading). To further explore a relation between exercise-induced change in sAA with brain and cognition, baseline and stress-induced (i.e., exercise, TSST) change in cortisol will be investigated as a potential factor in the analytical model. All participants provide written assent/consent (and legal guardians provide written informed consent) by a trained research technician in accordance with the Institutional Review Board of Northeastern University. The study was designed in accordance with the SPIRIT statement, details are provided in Fig. 1.

**Fig. 1 Fig1:**
[figure not shown]
SNEACY schedule of enrollment, interventions, and assessments

### Primary outcome

The primary outcomes are changes in cognitive performance following each of the three acute interventions. Specifically, we predict that exercise-induced phasic increases in SNS activity, indicated by sAA levels, will mediate the effect of a single bout of exercise on brain function (i.e., P3 amplitude and latency), cognition (i.e., executive control), and standardized achievement test performance (i.e., mathematics, reading).

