#### Neuroelectric assessment: electroencephalogram (EEG)

One of the primary aims of the SNEACY study is to examine the acute changes that occur in brain function following exercise intervention. Accordingly, on sessions 2, 3, and 4, children are fit with an EEG cap in order to measure brain activity before and after intervention. EEG activity is measured from 64 electrodes and 4 integrated bipolar leads for vertical and horizontal EOG (VEOG, HEOG), arranged according to the international 10–10 system using a Neuroscan Quik-cap (Compumedics, Inc., Charlotte, NC). EEG data is collected while cognitive tasks are completed.

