### Power and analytic strategy

A traditional power analysis was conducted to estimate the appropriate sample size necessary for detecting a mediating effect of sAA levels on the relationship between a single bout of aerobic exercise and acute changes in cognition given the inclusion of potentially confounding variables (e.g., age, sex, BMI, IQ, SES) based on a one-sided alpha of .01 to correct for multiple outcomes and a power of 0.8. For the total effect of exercise on the ERP and cognitive outcomes, an effect size was calculated from the results reported in Hillman et al. [9], which observed increased P3 amplitude, task performance, and scholastic achievement following acute exercise relative to rest in a sample of preadolescent children resulting in a moderate-to-large effect size (Cohen’s *d* = 0.79). Therefore, assuming a medium size of Cohen’s *f*2 = 0.15 for the total effect and 8 predictors (including exercise condition, subject ID, and covariates) in the regression model, power analysis indicate that a sample size of 82 participants will provide adequate power to detect the effects of a single bout of exercise on neuroelectric function and behavioral performance. For the mediation analysis, medium effect sizes [33] were assumed for both the direct effect of exercise on sAA levels (path a: coefficient = a) and the direct effect of sAA level on the outcomes controlling for treatment condition (path b: coefficient = b). Corresponding to Cohen’s [34] criteria for medium (13% of the variance) effect size, the values of a and b were set at 0.39. Applying the Sobel [35] first-order test, the indirect effect or the mediated effect of exercise on outcomes through sAA was indicated by the product of a and b and was tested. Empirical power results [36] showed that a sample size of *N* = 103 per study was required to detect the presence of mediation. Accordingly, we aim to recruit *N* = 120 to account for attrition.

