We will investigate whether the effect of the experimental conditions (*x*) on brain function, cognition, or academic achievement (distal *y* outcomes) is mediated by sAA and CORT baseline levels (*i*) and sAA change (*s*) using a path modeling framework (Mplus v8) and conventional model-to-data fit indices [37]. Each model will be adjusted for the set of potentially confounding variables (e.g., age, sex, BMI, IQ, SES). We will interpret significant direct effects on each outcome as supporting our hypotheses. We aim to incorporate the change process of sAA (*s*) and CORT (*s*) within the same model (allowing s and s to covary). We will utilize the most current and recommended practices [38, 39] for testing moderated mediation framework that leverages the stability of the entire sample for model estimation (causal structure); 5000 bootstrap draws will be run to collect the bias-corrected bootstrapped confidence intervals (95% CI) and significant indirect effects will be decomposed in Mplus output (identical to the Sobel test [35]). If mediation is found, subsequent tests of moderation will be conducted. To test the effect of the treatment condition (i.e., exercise, TSST-C, rest) on univariate continuous outcomes (brain function, cognition, academic achievement), three separate models will be tested using planned comparisons with imposed group invariance constraints. Group comparisons in sAA mean can be simultaneously compared (Is sAA larger in exercise compared to TSST-C and/or rest?), while also comparing benefits in the continuous outcomes regressed on sAA.

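### The primary outcome is stated in two ways with no deciding contrast, so the one-sided .01 has no fixed family and does not assure .05 control

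*Protocol article*

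**What the plan says.** The Primary outcome section opens with "The primary outcomes are changes in cognitive performance following each of the three acute interventions". Its next sentence makes the prediction one of mediation by sAA of the exercise effect on "brain function (i.e., P3 amplitude and latency), cognition (i.e., executive control), and standardized achievement test performance (i.e., mathematics, reading".

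On comparators, Summary of aims states: "The TSST and seated rest interventions serve as active and passive control conditions, respectively". Neither is ranked above the other. Under Power and analytic strategy, the condition effects on brain function, cognition and achievement are to be examined as follows: "three separate models will be tested using planned comparisons with imposed group invariance constraints". The same paragraph says that significant direct effects on each outcome will be taken as support for the hypotheses.

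The only multiplicity statement is in the power paragraph: "based on a one-sided alpha of .01 to correct for multiple outcomes and a power of 0.8". No divisor, family or family-wise level accompanies it. Indirect effects are to be judged by bias-corrected bootstrap 95% confidence intervals.

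The labels cover more than one score each. The abstract lists "Variables of interest include EEG data, accuracy and reaction time, academic achievement, and salivary alpha amylase". Two cognitive tasks (Go-NoGo and flanker) are run, each with two conditions or trial types, and EEG is recorded during both. The EEG section adds "One of the primary aims of the SNEACY study is to examine the acute changes that occur in brain function following exercise intervention".

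**The concern.** The two statements of the primary outcome are different hypotheses. A change in cognitive performance after a condition is a total effect on behaviour. A mediated effect on P3 or on an achievement score is neither a total effect nor, for P3 and achievement, cognitive performance in the first sentence's sense. With two unranked controls as well, the document does not say which result decides the trial. Exercise might beat rest but not the TSST, or help flanker reaction time but not Go-NoGo accuracy, and the plan does not say what would then be concluded.

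The .01 level is presented as the correction for this multiplicity. A correction works only for a defined family, and the family that the document describes can be several times larger than the one .01 would cover.

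**Working it through.** **1. The plan's own level.** The second primary-outcome sentence carries five labels, and .05/5 = .01. Five independent tests at .01 give 1 − .99^5 = .049; with common correlation .5 the figure is .040, and with .8 it is .028. So .01 is adequate for five tests, each done once. Had the intended one-sided family level been .025, .01 would cover only two tests (.025/.01 = 2.5).

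**2. Number of condition contrasts.** Under Wide Range Achievement Test 4, each child takes the WRAT-4 after rest and after only one of exercise or TSST. The two exercise–TSST achievement contrasts therefore cannot be made within child and are removed.

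- Labels as written: 5 × 2 controls − 2 = 8.
- Both tasks, each with P3 amplitude, P3 latency, accuracy and reaction time, plus two achievement scores: (2 × 4 + 2) × 2 − 2 = 18.
- Each task also split by its two conditions: (2 × 2 × 4 + 2) × 2 − 2 = 34. This is an upper bound.

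**3. Family-wise error at one-sided .01.** Setup: every null hypothesis true, rejection at z > 2.326, outcomes with common correlation r, and the two contrasts on an outcome correlated .5 because they share the exercise condition.

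At r = 0 there is a closed form. For one outcome with both contrasts, the chance of at least one rejection is .01 + .01 − .0013 = .0187. With k such outcomes plus two achievement scores tested once, the error is 1 − (1 − .0187)^k × .99². Putting k = 3, 8 and 16 gives .074, .157 and .275. The other columns are simulated; repeat runs agree to about .002.

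| Tests | r = 0 | r = .5 | r = .8 |
|---|---|---|---|
| 8 | .074 | .06 | .046 |
| 18 | .157 | .11 | .067 |
| 34 | .275 | .165 | .089 |

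**4. If the contrast were settled.** With one deciding contrast, or a rule that exercise must beat both controls, the error is at most .01 per endpoint. Five endpoints then give at most 5 × .01 = .05. Ten endpoints (both tasks, 2 × 4 + 2) give up to 1 − .99^10 = .096 if independent. Fixing the contrast alone is not enough; the endpoint list must be fixed too.

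**5. Level in the mediation analysis.** A 95% interval is a two-sided .05 test, or .025 in the favourable direction, which is 2.5 times the stated .01. At nominal coverage, five independent intervals give 1 − .95^5 = .226 for a false finding in either direction and 1 − .975^5 = .119 in the favourable one.

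The mediation sample size points the same way. With a = b = 0.39 and unit residual variances, the Sobel formula is N = 2 × ((z_alpha + z_power)/0.39)². At two-sided .05 this is 2 × ((1.960 + 0.842)/0.39)² = 103.2, the article's 103. At one-sided .01 it is 2 × ((2.326 + 0.842)/0.39)² = 132. A simulated Sobel test gives about 90 and 115 instead, so the match depends on the formula, but neither method returns 103 at one-sided .01.

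**The case against.** A journal article condenses the protocol, and the choice of trial type, score or hierarchy may properly sit in an analysis plan that is not shown. That disposes of any complaint about missing detail alone. It does not dispose of two different primary-outcome statements, two unranked comparators, or a .01 level that the interval rule does not follow, all of which are in the article itself.

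Several stronger readings are tempting and are not supported:

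- **That the article sets .01 for exactly five tests at a .05 family level.** It states neither number; both are inferred.
- **That success on any one test counts as a win.** No such rule is written. The sentence on significant effects on each outcome could even mean that all are required. The attribution argument in Summary of aims, which sets exercise apart from expectancy, stress and raised heart rate, reads naturally as needing exercise to beat both controls. With five endpoints, that reading keeps the error within .05. The fault is that the document does not choose.
- **That the question "Is sAA larger in exercise compared to TSST-C and/or rest" shows the outcome contrast to be undecided.** It concerns the mean of the mediator, not a primary outcome.
- **That 34 or more tests are planned.** The task sections describe how the tasks are built, not separate analyses of each trial type.
- **That the rates above apply to the mediation tests.** They are for condition contrasts. The Sobel test is conservative under the null: at one-sided .01, its simulated per-test rate is about .002 when path a is real (assumed z about 4) and b = 0, so ten independent tests give about .02. That protection does not carry over to the bootstrap 95% intervals, which are the stated decision rule.

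It also stands that the eight-test case falls slightly below .05 at correlation .8. Loss of control is not shown at the low end.

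**Conclusion.** The point holds as one of undefined primary inference and unassured error control. For the condition contrasts, family-wise error at one-sided .01 is about .06 for 8 tests (.046 to .074 over outcome correlations .8 to 0), .11 for 18 (.067 to .157) and .165 for 34 (.089 to .275). Once both tasks are tested against both controls, it exceeds .05 at every correlation examined.

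This rests on an inferred .05 family level, on tests that can each support the claim, and on outcome correlations that the document does not give. It does not establish that the trial's error rate is inflated by any particular factor, because that depends on a decision rule the article does not state. Separately, and without those assumptions, the .01 of the power section is not the level at which the mediation analysis will be read.

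**What to change.** Data collection is described as ongoing, so these changes can be made before data lock:

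- In Primary outcome, give a closed list of endpoints, with task, condition and score for each of the five labels. The choice is the investigators'; one prespecified flanker measure per label would be an example.
- Name one deciding contrast (exercise versus rest matches the source of the effect size in the power section), or state that exercise must beat both controls. Otherwise apply Holm across all retained primary tests.
- Test mediation on an endpoint only after its exercise effect is significant.
- Use one alpha in the power section and for the intervals. One-sided .01 corresponds to a 98% two-sided interval.
- Label all other measures and contrasts secondary.
- State that WRAT-4 exercise–rest comparisons use only the children tested after exercise, and that a both-controls rule cannot be applied within child to achievement. If the split were even (an assumption), about half of 103 would contribute and the standard error would rise by about √2 = 1.41.

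The cost is a few sentences and no new data, but some comparisons lose confirmatory status. Carrying .01 into the mediation test also costs power: at N = 103 the Sobel formula gives about .68 (.71 by simulation), and at the recruitment target of 120 about .76 (.83). The power paragraph should report this.

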### Recruitment

Recruitment for SNEACY began in February of 2019, and the goal is to enroll 103 (60 female) children by December 2021. Participants are typically developing, healthy 9–10-year-old children from the Greater Boston, MA region. The goal for recruitment of racial and ethnic minorities is in proportion to the demographic representation in Boston, MA (77.4% Caucasian, 13.2% African American, 17.4% Latino/Hispanic, 5.4% Asian, 1.2% Native American, 0.2% Native Hawaiian and Other Pacific Islander, and 2.5% multiracial). Participant recruitment occurs through local media outlets, community websites, parent group website, University list-serves, contact with local youth organizations, and fliers. To recruit racial and ethnic minorities, diverse neighborhoods in the greater Boston area will be a focus of recruitment, particularly in terms of community centers, libraries, and local newspapers. Fliers contain a general introduction of the research and the contact information of the research team so that interested individuals initiate contact with the research team directly. Recruitment, enrollment, and randomization occur continually.

### Eligibility

The eligibility criteria were designed to recruit children who are typically developing, generally healthy, and able to safely exercise. These criteria were developed to ensure participant safety, as well as a maximal generalization to children broadly (see Table 1).

**Table 1 Tab1:** Inclusion-exclusion criteria for SNEACY participants

Inclusion	Exclusion
1. Parental/guardian consent and participant assent.	Non-consent of guardian or non-assent of participant.
2. 9–10 years of age.	Above/below 9–10 years of age.
3. Capable of performing exercise based on PAR-Q.	Any physical disability that prohibits exercise.
4. Normal/average IQ or above (i.e., > 85).	IQ < 85.
5. Participants must have not yet reached, or be in the earliest stages, of puberty, as measured by a modified test of the Tanner Staging System (Tanner score < 2).	Tanner score > 2.
6. No prior diagnosis of cognitive or physical disability, including ADHD, uncontrolled asthma, epilepsy, chronic kidney disease, and dependence upon a wheelchair/walking aid.	Prior diagnosis of cognitive or physical disability, including ADHD, uncontrolled asthma, epilepsy, chronic kidney disease, and dependence upon a wheelchair/walking aid.
7. Free of any type of anti-psychotic, anti-depressant, anti-anxiety medication as well as medications used for ADD/ADHD (use of any anti-psychotic, anti-depressant, anti-anxiety, and ADD/ADHD medications).	Use of any type of anti-psychotic, anti-depressant, anti-anxiety medication as well as medications used for ADD/ADHD (use of any anti-psychotic, anti-depressant, anti-anxiety, and ADD/ADHD medications).
8. Normal or corrected-to-normal vision based on the minimal 20/20 standard in order to complete the cognitive task (below 20/20 vision).	Normal or corrected-to-normal vision below 20/20 vision.
9. Able to speak and read English.	Not fluent in English.

